#### Sensitivity analysis

In order to assess the sensitivity of the results due to the assumption of a missing mechanism, we will conduct complete case analysis using the inverse probability weighted generalized estimating equation (IPW-GEE), assuming the missing data will be missing at random given observed outcome and time-dependent covariates. IP weights at each assessment will be estimated by pooled logistic models for the probability of not dropping-out from the follow-up, conditional on the measured risk factors and groups; weights are the reciprocal of the estimated probability. Additionally, we will use IPW-GEE to assess effect of the intervention when the definition of abstinence is changed: (1) complete abstinence from all substances including the non-primary abused drug and alcohol and (2) the longest duration of consecutive abstinence in the past 28 days instead of the intervention period (56 days).

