### Sample size

Sample size is assumed for two primary outcome variables (relapse risk and the longest duration of abstinence) to detect a medium effect size of *d* = 0.4 based on previous studies for drug users. As for the first primary outcome (relapse risk), the effect size between pre and post intervention was *d* = 0.39 in a study conducting a relapse prevention program in Japan [60]. On another primary outcome (the longest duration of abstinence), the effect size between the intervention group and control group after the intervention was reported as *d* = 0.45 in a study conducting for computer-assisted cognitive behavioral therapy [19]. We estimated a sample size of 100 per group (total 200), assuming α = 0.05 and a power (1 - β) = 0.08. Attrition rate and non-completion rate was reported as relatively high (about 10–45 %) in previous studies of computer-assisted and web-based intervention for drug users [11, 19, 61]. However, we did not include additional samples because we expect a low attrition rate because all the participants will be outpatients motivated to seek treatment and we will send email reminders to follow up.

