### Statistical analysis

#### Primary analysis

The primary analysis for the SRRS score will be on an intention-to-treat basis, using mixed-effect models. We will use all obtained data at the 2, 5 and 8 months assessment without imputation, assuming the missing mechanism will be at random given observed data within the groups. We will include the following variables as fixed effects: the group, time, the baseline scores and the interaction of group and time. Time will be coded as months after the baseline assessment, giving values of 0, 2, 5 and 8. We will also include random effects of participants for intercept and time. The effect of the intervention will be assessed by a test of hypothesis that a time and group interaction equals 0. To help interpretation in terms of effect size, Cohen’s *d* between groups and 95 % confidence intervals will be calculated at each assessment point; the values of 0.2, 0.5 and 0.8 are considered as small, medium and large effect, respectively [62]. The longest consecutive abstinent days from the primary abused drug during intervention will be compared using *t*-test. Also, we will calculate a Cohen’s *d* for the longest consecutive abstinent days.

When there are significant differences in both of the two primary outcomes between groups with a level of 5 % in the two-sided test, the intervention will be considered effective. Analyses will be conducted using SPSS Statistics Ver. 22.

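### The planned check on the missing-data mechanism assumes missing at random again, so its agreement with the primary SRRS model is not evidence of robustness to the mechanism

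*Protocol article*

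**What the plan says.** Under Primary analysis, the SRRS is analysed by intention to treat with a mixed model containing group, time, baseline score and group by time. It uses all obtained follow-up data "without imputation, assuming the missing mechanism will be at random given observed data within the groups". The test is of the group-by-time interaction. Longest consecutive abstinence is compared by t-test, and both outcomes must be significant for the intervention to be called effective.

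Under Sensitivity analysis, the purpose is given as "In order to assess the sensitivity of the results due to the assumption of a missing mechanism". The method is a complete-case IPW-GEE, "assuming the missing data will be missing at random given observed outcome and time-dependent covariates". Its weights come from pooled logistic models for remaining in follow-up, "conditional on the measured risk factors and groups; weights are the reciprocal of the estimated probability". The section then adds that "we will use IPW-GEE to assess effect of the intervention when the definition of abstinence is changed"; those further analyses vary the outcome definition, not the missing-data mechanism.

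Under Sample size, the article notes that "Attrition rate and non-completion rate was reported as relatively high (about 10–45 %) in previous studies" of comparable interventions. It adds no participants for this because it expects low attrition.

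**The concern.** The stated purpose is to probe the missing-mechanism assumption, but the method keeps that assumption. If the mixed model and the IPW-GEE agree, a reader of the results will take it that the finding survives doubt about why data are missing. It would show only that two MAR models with different conditioning sets agree.

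The mechanism left out is plausible on the article's own account. All outcomes are self-reported (Discussion), and the questionnaires are completed on the same website that delivers the programme (Data collection procedure). The Background describes strong stigma and a zero-tolerance policy. A participant who relapses may stop using the site, and the outcome data are then lost with the engagement. If that happens after the last observation, nothing measured predicts it fully.

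**Working it through.** **1. The two assumptions side by side.** Let R be response at a visit and Y the SRRS score that would be recorded there.

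- Primary mixed model: given the observed SRRS data and group, R does not depend on the unseen Y.
- IPW-GEE: given the observed SRRS data, group and measured time-dependent covariates, R does not depend on the unseen Y.

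The second list is longer, and that is the only change. Relapse already visible in calendar entries or an earlier SRRS score can enter the weights. Relapse after the last observation cannot. The gap can be long: Trial design places follow-up at 8, 20 and 32 weeks, so the last two intervals are 20 − 8 = 12 and 32 − 20 = 12 weeks, while the weekly calendar deadlines are described for the 8-week intervention period.

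**2. The plan's own figure.** With d = 0.4, two-sided α = 0.05 and power 0.80 (printed as 0.08), n = 2(1.960 + 0.842)² / 0.4² = 98.1, so 99 per group. The stated 100 is reproduced; power at 100 is 80.4% by noncentral t. This supplies the scale used below and is not itself in dispute here.

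**3. Illustrative shift at one visit.** If a fraction m of an arm is missing and truly δ worse than MAR predicts, the between-arm difference is off by δ_E·m_E − δ_C·m_C. Equal values in the two arms cancel. With an assumed δ_E = 0.5 SD and δ_C = 0:

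- m = 10%: 0.5 × 0.10 = 0.05 SD
- m = 20%: 0.5 × 0.20 = 0.10 SD, a quarter of 0.4

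**4. Illustrative tipping point.** Assume an MAR estimate of exactly 0.40, SD 1, 100 randomised per arm, the same fraction missing in each arm, and the shift in the e-SMARPP arm only. With standard error √(2/[100(1 − m)]), significance is lost when δ exceeds (0.40 − 1.96·SE)/m:

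| m | 1.96·SE | tipping δ (SD) |
|---|---|---|
| 10% | 0.292 | 1.08 |
| 20% | 0.310 | 0.45 |
| 30% | 0.331 | 0.23 |
| 45% | 0.374 | 0.06 |

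**5. Simulation.** Assumptions: no true effect, 100 per arm, baseline to follow-up correlation 0.5, about 30% dropout per arm, one follow-up, 2000 replicates, and baseline-adjusted regression standing in for the mixed model.

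- e-SMARPP dropout driven by the observed baseline: bias +0.005 SD for both methods; rejection 4.8% (regression) and 3.8% (IPW).
- e-SMARPP dropout driven by the unseen follow-up score: bias −0.20 SD (regression, rejection 28%) and −0.21 SD (IPW, rejection 24%), both favouring e-SMARPP.

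In the second case the methods agree and both are wrong. IPW was given no time-dependent covariate, so part of that agreement is built in. The simulation shows that agreement can mislead, not how often it would.

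**6. Limit of steps 3 to 5.** They concern a mean difference at one visit. The planned test is group by time, and its distortion depends on how missingness and the shift change across visits.

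**The case against.** **The IPW-GEE is not empty.** It brings in time-dependent covariates, so relapse recorded before dropout can be allowed for, and its MAR assumption is stated openly. This stands. A reader might infer that the analysis is worthless or that all relapse-driven dropout goes unexamined; the text does not support that.

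**An unseen analysis plan may hold a tipping-point analysis.** Possibly, so its absence from a condensed article is not the point. The point is that the article names a purpose and fixes a method that cannot fully meet it.

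**Outcome collection is matched between arms.** Monday calendar reminders go to both arms (Intervention group, Control group), and follow-up invitations, reminders, postcards and prepaid cards are the same for all (Data collection procedure). Only session reminders and tailored feedback are one-sided. Nothing in the article shows that e-SMARPP dropouts would fare worse than control dropouts, and an equal shift with equal missingness cancels. This stands, and it makes the one-arm shift a stress case.

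**The second primary outcome.** A reader might infer that the t-test runs on whoever marked the calendar and that weighting never reaches this outcome under its main definition. Neither is stated. Abstinent days come from the calendar and TLFB together (Primary outcome, Abstinence), so an unmarked day is not automatically missing, and the opening purpose of the Sensitivity analysis section refers to results generally.

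**Attrition may be low.** At 10% missing, the illustration needs a shift of about 1.1 SD to lose significance. The 45% upper figure mixes attrition with non-completion, and not finishing a programme is not a missing outcome. Both points stand.

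**Conclusion.** The point holds in limited form. The analysis offered as the check on the mechanism is a second MAR analysis with a wider conditioning set. It can address relapse recorded before dropout but not unobserved relapse that causes the missing assessment, so agreement with the primary model must not be presented as robustness to the mechanism. This follows from the article's own wording and needs no assumption about attrition.

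The size is not established. The 0.05 and 0.10 SD shifts rest on an assumed 0.5 SD worsening in one arm at one visit; the practical importance depends on attrition actually seen. A reader might go further and conclude that more than half of the planned effect could be artefact, taking 45% missing (0.5 × 0.45 = 0.225 SD against 0.4). The article does not support that, since the 45% is not a pure attrition figure and the shift is not the tested quantity. It is worth correcting before unblinding, because the remedy is cheap and the trial's success rule needs both primary outcomes.

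**What to change.** 1. Relabel the IPW-GEE as an alternative MAR analysis, and state that it does not examine departures from MAR.
2. For the SRRS, add multiple imputation with a delta adjustment. Worsen imputed scores by increasing amounts in both arms, and separately in the e-SMARPP arm alone. Report the delta at which the planned group-by-time test loses significance, so that readers can judge its plausibility against the attrition observed.
3. For longest abstinence, add a sensitivity analysis in all randomised participants in which days still unrecorded after both the calendar and TLFB count as use, in both arms. Describe it as a conservative bound: one such day can break a streak (with day 28 of 56 unrecorded, the remaining runs are 27 and 28 days, so the longest falls from 56 to 28). Applying the rule to one arm only would penalise incomplete recording rather than relapse and is best avoided.

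The cost is a small amount of extra prespecified analysis. No new data, visits or participants are needed, and the primary analyses stay as they are.

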#### Subgroup analysis

The effect of the intervention will be assessed by subgroups because the effect may vary depending on specific population. The participants will be divided by the primary abused drug (i.e., methamphetamine, NPS and prescription drugs), sex, severity of drug addiction (DAST-20 score: 0–5, 6–15, 16–20), the duration of abstinence at the baseline assessment (<1 month, 1–6 months, 7–12 months) and whether receiving face-to-face behavioral therapy or not.

#### Cost effectiveness analysis

Health economic evaluation will be undertaken using data generated within the present trial, to provide information on the ‘value’ of allocating resources to the e-SMARPP (plus usual care) strategy over self-monitoring (plus usual care). The research question regarding the economic evaluation is, ‘Is e-SMARPP potentially a cost-effective means of helping abuse drug users to increase abstinent days? Specifically, we will employ a cost-effectiveness analysis (CEA) framework, and the results of analysis will be summarized as an incremental cost-effectiveness ratio (ICER). A within-trial analysis will evaluate cost-effectiveness from a patient and institutional perspective. Sensitivity analysis will be undertaken for parameter uncertainty of benefits measures and assumptions to calculate average costs. Subgroup analysis will be of great interest to make policy recommendations for a more targeted approach. Subgroups categorized by variables set in the main trail analysis, e.g., types of abuse drug primarily used, will be adopted for this subgroup analysis in an economic evaluation.

### Data monitoring

The research members who have an e-SMARPP account (AT, YM, NK and TM) will monitor the data. The first author (AT) will manage participants’ progress and completion of the intervention and the follow-up assessments. The members will share information about recruitment progress and data collection every month.

Information of adverse events including hospitalization, arrest and death will be collected from the participants’ primary doctor during the intervention. Additionally, participants will be asked about subjective harmful effect (i.e., craving, mental distress) when they use e-SMARPP at the follow-up assessment (T2).

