## Methods

### Trial design

Figure 1 shows the design of this study and participant flow. This study is a two-arm (allocation ratio is one to one), parallel-group, non-blinded and multicenter randomized controlled trial. Eligible participants are asked to complete the baseline assessment and are randomly allocated to either the intervention group or the control group. All participants in both groups will be provided a login/password with instructions about how to access the website and use e-SMARPP during the study. The participants in the intervention group can access the complete contents of e-SMARPP, while the control group can access a part of it: self-monitoring. Each individual access account is tied to either group, and as such participants can use e-SMARPP content included in their group only. Web-based follow-up assessments are conducted at 8, 20, 32 weeks after the baseline assessment.

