#### Intervention group

Participants who are assigned to the intervention group are provided access to the complete contents of e-SMARPP, including six sessions for cognitive behavioral relapse prevention and web-based self-monitoring. They are expected to complete each session over a week in sequence order by each deadline (each Sunday). For an 8-week intervention period, they are expected to complete a total six sessions, but they have a 2-week grace period and are allowed to progress at their own pace. If they do not complete a session, the session will be carried over to the next week. Participants will be expected to record their daily situation of drug use on the web-based self-monitoring calendar by each deadline (each Sunday). If they do not go through an expected session and/or self-monitoring by each deadline, a researcher will send an e-mail reminder on the next day (Monday).

Participants continue to receive outpatient treatment as usual, including medication, face-to-face group or individual psychosocial treatment programs and counseling by psychologists and/or social workers. Provided treatment depends on individual condition. Even if participants stop receiving outpatient treatment or change their primary doctor and hospital, the web-based intervention will not be cancelled.

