##### Cost of substance use and treatment use

Total cost of alcohol and drug use in the past month will be asked separately. In Japan, methamphetamine is more expensive than other drugs (above 10,000 yen for use of methamphetamine several times). New psychoactive substances (NPS) are relatively cheap (about 2000 to 5000 yen for one package).

Cost of psychiatric treatment use in the past 6 months will also be assessed. We will ask about frequency and period of psychiatry hospitalization and outpatient treatment, frequency of use of emergency room, total cost of prescription drugs, frequency and period of specialized outpatient treatment for drug addiction, the participant’s income and amount of time required to receive one outpatient treatment including travel time. We will calculate total psychiatric medical cost using the annual report of medical costs by diseases and treatment [48].

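### Serious events are collected as adverse events only from the primary doctor and only for 8 of 32 weeks, and no route is described for arrest, death or subjective harm after T2

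*Protocol article*

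**What the plan says.** The Data monitoring section of the protocol article fixes both the source and the window for serious events: "Information of adverse events including hospitalization, arrest and death will be collected from the participants’ primary doctor during the intervention". Where that sentence meets the next, the text reads "primary doctor during the intervention. Additionally, participants will be asked about subjective harmful effect": the one participant-reported element is a question at T2 on subjective harm from using the program, with craving and mental distress as the examples.

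The Intervention group section gives the length of that window: "For an 8-week intervention period, they are expected to complete a total six sessions". The Trial design section sets the follow-up: "Web-based follow-up assessments are conducted at 8, 20, 32 weeks after the baseline assessment". On participants who leave care, the Intervention group section says: "Even if participants stop receiving outpatient treatment or change their primary doctor and hospital, the web-based intervention will not be cancelled".

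One later item bears on harms, although it is listed as an outcome. Under Cost of substance use and treatment use the article says: "We will ask about frequency and period of psychiatry hospitalization and outpatient treatment, frequency of use of emergency room". The recall window is stated there too: "Cost of psychiatric treatment use in the past 6 months will also be assessed". Table 2 schedules this item at baseline and T4 only.

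**The concern.** The article itself names hospitalization, arrest and death as the events to collect, yet collects them as adverse events only while the intervention runs. Efficacy is followed four times as long (32 weeks against 8).

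The source is also tied to something the trial expects to influence. A primary doctor can report only on patients still seen. The article foresees that some participants will stop outpatient care and keeps them in the web intervention, but names no other source of serious events for them. The Objectives and hypotheses section predicts better treatment retention in the e-SMARPP group, and retention is a secondary outcome in Table 2. If that prediction is right, doctors would be better placed to report events in the e-SMARPP arm than in the control arm, and a comparison of event counts would partly reflect who was still being seen.

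At stake are the completeness and balance of the harms report. The two primary outcomes and their analysis are not affected.

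**Working it through.** The article gives no event rates and no planned harms figure, so there is nothing of its own to reproduce. The check is arithmetic on the schedule, then a comparison of what each route covers.

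**Inputs.** Intervention: 8 weeks (Intervention group). Last follow-up: 32 weeks (Trial design), also given as 8 months (Data collection procedure, Table 2). Recall window of the T4 medical-use item: 6 months (Cost of substance use and treatment use).

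**Time without described adverse event collection.** 32 − 8 = 24 weeks; 24/32 = 75% of follow-up.

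**Reach of the T4 recall item.** One month is 52.1775/12 = 4.348 weeks, so 6 months is 26.09 weeks.
- T4 at week 32: recall starts at 32 − 26.09 = week 5.9, before the intervention ends.
- T4 at 8 calendar months: recall starts at month 8 − 6 = 2, and 2 × 4.348 = week 8.7, which leaves about 0.7 weeks after week 8 uncovered.

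On either reading, this item spans almost all of the post-intervention period for participants who answer at T4.

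**Coverage by event type.**

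| Event | Weeks 0–8 | After week 8 |
|---|---|---|
| Psychiatric hospitalization | Primary doctor | Self-report at T4, as a cost item, respondents only |
| Emergency room use | Not named as an adverse event | Self-report at T4, as a cost item, respondents only |
| Arrest | Primary doctor | None described |
| Death | Primary doctor | None described |
| Subjective harm from the program | Participant, once at T2 | None described |

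The emergency procedure under Research ethics and approval does not fill the empty cells. It applies only if a researcher happens to learn of an emergency through e-SMARPP, and it leads back to the primary doctor.

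**Participants who leave care.** Someone who changes doctor still has a primary doctor, so the stated source still exists. Someone who stops outpatient care altogether has none. For that group, no route to arrest or death is described even in weeks 0–8.

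**Difference between arms.** The number of events affected would depend on retention by arm and on event rates among those who leave. The article gives neither, so size and direction cannot be computed.

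**The case against.** The strongest case on the other side is that tying adverse event collection to the 8 weeks of exposure is a defensible choice for a web-based behavioural adjunct, that the article states it openly, and that detailed safety procedures usually sit in a fuller protocol. This carries some weight. But the article does not leave the window and source to another document; it states both, so they can be assessed as written.

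Several stronger readings are tempting, and the article does not support them.
- A reader might infer that the doctor is the only source of any harm. That is not so: participants are asked directly at T2, and someone who has left care can still answer.
- A reader might infer that all harms after week 8 are lost, or that serious-event ascertainment covers only 25% of follow-up. That is too strong for psychiatric admissions and emergency room use, which the T4 item largely recovers among respondents. Relapse risk, abstinence and quality of life are also measured at T3 and T4, so some deterioration would show there, although these measures do not ask whether the program caused harm.
- A reader might infer that anyone who leaves the recruiting clinic loses the doctor source. The text refers to the participant's primary doctor, so only stopping care removes it.
- A reader might hold it against the trial that it cannot answer the Discussion's question about safety in users without other treatment. That question concerns a different, future population. This trial enrols outpatients, and a longer window would not answer it.

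It can also be argued that unequal reporting by arm is speculation, because staff at the recruiting institutions are blinded. Blinding does not help if patients stop attending, and the hypothesised retention effect is the trial's own reason to expect a difference. The argument does stand on one point: no difference has been shown.

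**Conclusion.** The point holds within these limits. Hospitalization, arrest and death are collected as adverse events from one source for 8 of 32 weeks. For the other 24 weeks (75%), arrest, death and subjective harm have no described route, and psychiatric admissions and emergency room use appear only as a T4 cost item from respondents. Participants who stop outpatient care have no named alternative source of serious events. Unequal ascertainment between arms is a possibility grounded in the trial's own retention hypothesis; its size and direction are unknown.

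This rests on the article as published. If a fuller protocol describes adverse event collection after week 8, the two should be reconciled. The effectiveness conclusion is untouched, so this is an inexpensive improvement to the harms data and does not threaten the trial's validity.

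**What to change.** - Add hospitalization and arrest items to the existing T2, T3 and T4 web questionnaires, and subjective-harm items to T3 and T4. The baseline questionnaire already asks about past arrest, so that item needs little adaptation.
- Ask the recruiting institutions once for known deaths, admissions and arrests up to 8 months. Questionnaires cannot capture deaths, and the request can be retrospective for participants already past T3 or T4.
- Use the T4 hospitalization data in the harms report as well as in the costing.
- Report events by arm, with the follow-up time covered and the number of participants who had neither a doctor nor a questionnaire as a source.

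The cost is slightly longer questionnaires, one data request per site and an ethics notification. Treatment, primary outcomes and sample size do not change. The remaining limitation is that events in non-responders outside care may still be missed, which is why the number without a source should be reported.
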